**November 2011**

# ABBREVIATIONS

| ART | Antiretroviral Therapy |
| --- | --- |
| ATIC | AIDS Treatment Information Center |
| CHOICE | Choosing Interventions that are Cost-Effective |
| CQI | Continuous Quality Improvement |
| DALY | Disability Adjusted Life Year |
| DHS | Demographic and Health Survey |
| EA | Enumeration Area |
| HCI | Health Care Improvement Project |
| IDI | Infectious Diseases Institute |
| IDT | Infectious Diseases Training |
| IMAI | Integrated Management of Adult and Adolescent Illness |
| IMCI | Integrated Management of Childhood Illness |
| I-TECH | International Training and Education Center on Health |
| MCT | Multi-disciplinary Clinical Training |
| MLP | Mid-level practitioner |
| OSS | On-site support services |
| PEPfAR | President’s Emergency Plan for AIDS Relief |
| SOMREC | School of Medicine Research and Ethics Committee |
| U5 | Child less than 5 years |
| UBOS | Uganda Bureau of Statistics |
| USAID | United States Agency for International Development |
| WHO | World Health Organization |

# DEFINITION OF OPERATIONAL TERMS

Efficacy - Efficacy describes how well treatment works in ideal circumstances

Effectiveness - Effectiveness describes how well treatment works in real life. Treatments may work less well in practice than clinical settings due to patient non-compliance and co-morbidity

Cost-effective - Compares incremental cost to incremental effectiveness, e.g. $/life years saved from intervention vs. usual care

Incremental Cost-Effectiveness Ration (ICER) – ICER is the ratio of the difference in cost between two group of subjects and the difference in effectiveness between two groups of subjects.

Task shifting - According to WHO, task shifting is the rational redistribution of tasks among health workforce teams, “Specific tasks are moved, where appropriate, from highly qualified health workers to health workers with shorter training and fewer qualifications in order to make more efficient use of available human resources for health.”

Mid-level practitioners – These practitioners are defined in this proposal as clinical officers, nurses, and midwives.

Clinical officers – These non-physician clinicians have a secondary school education (13 years), three years of pre-service training and two years of internship.

Registered Nurses or Midwives – These nurses and midwives have a secondary school education (13 years) and three years of pre-service training

Enrolled Nurses or Midwives – These nurses and midwives have a secondary school education (13 years), and one and one-half years of pre-service training.

Nurse-midwives - These double-trained professionals have a secondary school education (13 years) and four and one-half years of pre-service training.

TABLE OF CONTENTS

[**ABBREVIATIONS 2**](#__RefHeading___Toc244140755)

[DEFINITION OF OPERATIONAL TERMS 3](#__RefHeading___Toc244140756)

[TABLES, FIGURES & BOXES 5](#__RefHeading___Toc244140757)

[ABSTRACT 6](#__RefHeading___Toc244140758)

[PREFACE 7](#__RefHeading___Toc244140759)

[CHAPTER ONE: INTRODUCTION 8](#__RefHeading___Toc244140760)

[1.1 Introduction 8](#__RefHeading___Toc244140761)

[1.2 Literature review 8](#__RefHeading___Toc244140762)

[CHAPTER TWO: RESEARCH PROBLEM 10](#__RefHeading___Toc244140763)

[2.1 Problem Statement 10](#__RefHeading___Toc244140764)

[2.2 Significance 10](#__RefHeading___Toc244140765)

[2.3 Research Question 11](#__RefHeading___Toc244140766)

[2.4 Objectives 11](#__RefHeading___Toc244140767)

[2.4.1 General ‘ 11](#__RefHeading___Toc244140768)

# ABSTRACT

This evaluation aim is to investigate a cost-effective way to build capacity for the care and prevention of infectious diseases among mid-level practitioners in sub-Saharan Africa. Classroom based training continues to be the dominant form of training, despite evidence that suggests that on-site support (OSS) is more beneficial. Definitive evidence that on-site support is the most effective way to deliver the required outputs and related outcomes is still lacking. IDCAP will provide two interventions that integrate training in TB, HIV/AIDS and malaria as well as other infectious diseases, and the effects will be studied.

**Infectious Disease Training (IDT)** - An integrated core curriculum for MLP in the comprehensive care and prevention of infectious disease, delivered to 72 MLP from 36 health facilities at IDI in three sessions for a total of five weeks with extensive clinical sessions.

**On-Site Support Services (OSS)** – CQI activities and a set of responsive Multidisciplinary Clinical Training (MCT) modules for use at the clinic level with teams of medical officers, clinical officers, nurses and midwives, laboratory technicians and records keepers will be sequentially delivered to the 36 facilities in two phases. Sites will be randomly assigned to either Phase 1 or 2.

The evaluation of the capacity-building program will assess the impact of IDT on individual performance and impact of OSS on cost, clinic performance and health outcomes, and definitively test whether or not the incremental impact of on-site support services relative to classroom training alone can be cost-effective. The four alternative hypotheses are:

1. An Integrated IDT course for mid-level practitioners is effective at building the skills required to perform key clinical tasks at acceptable standards
2. Onsite Multidisciplinary Team training and Continuous Quality Improvement activities (or On-Site Support- OSS) significantly improve clinic performance
3. OSS activities are cost effective
4. After monthly OSS for nine months during Phase 1 at Phase 1 sites, bi-monthly OSS for six months has an additional effect on facility performance

For hypothesis 1, the unit of analysis will be the individual trainee. The effect of IDT on capacity and practice will be measured with a pre/post comparison and by comparing the performance of the trainees at the end of the training program to an objective standard.

For hypotheses 2-4, the unit of analysis will be the site. The effect of OSS on cost, clinical performance and health outcomes will be measured by a comparison of Phase 1 and Phase 2 sites.

**Significance**: IDCAP will provide a model of an integrated capacity-building package for the care and prevention of infectious disease in Uganda and Africa at large. In Uganda, the 72 trained MLP and 432 health professionals at 36 sites will serve about 17% of Uganda’s population. The evaluation will contribute to current literature on the role of MPL in the management of infectious diseases and cost effective approaches to capacity building of MLP. Results will inform donors and governments on investments in human resource development in the health sector.

# PREFACE

The IDCAP proposal was submitted to the Bill and Melinda Gates Foundation three times beginning in spring 2007. The final version was submitted in March 2008 and approved for funding in November 2008. The proposal followed the Foundation’s format and was organized around five main activities, rather than the format of scientific proposals submitted to organizations such as the United States National Institutes of Health.

IDCAP is an evaluation of a training and quality improvement program. At the time the proposal was submitted, it was not envisioned that the evaluation would require human subjects/ethics committee review. The University of Washington’s Humans Subjects Review Committee made a similar determination.

In January 2009, the Uganda National Committee on Science and Technology (UNCST) recommended that we submit IDCAP so that they could review the distinction between quality improvement and research in more detail. As part of that process, the School of Medicine at Makerere University Research Ethics Committee (SOMREC) is also respectfully requested to review IDCAP. This proposal was prepared to comply with a SOMREC outline for research proposals.

# CHAPTER ONE: INTRODUCTION

## 1.1 Introduction

Considerable progress continues towards increasing access to anti-retroviral therapy (ART) in resource-limited settings. WHO, UNAIDS, and UNICEF recently estimated that 1.3 million people have access to ART in Sub-Saharan Africa, or 28% of people with HIV living there who need ART.[[1]](#endnote-2) These accomplishments required training of health professionals, among other efforts to strengthen health systems. For example, the United States’ Presidents Emergency Plan for AIDS Relief supported the training of 154,000 health professionals in ART from 2004 to 2007.[[2]](#endnote-3) The greatest challenge to increasing access to ART however, is the shortage of trained health care professionals.Error: Reference source not found[[3]](#endnote-4) [[4]](#endnote-5) [[5]](#endnote-6)

##

## 1.2 Literature review

**Mid-Level Practitioners (MLP) are emerging as the ideal clinicians in Africa.** In 2006, the Infectious Diseases Institute (IDI), in collaboration with the Ugandan Ministry of Health (MOH) conducted a national HIV/AIDS Training Needs Assessment which revealed that responsibilities usually reserved for a doctor, such as prescribing, are often passed on to clinical officers and nurses who report feeling insufficiently trained to carry out such activities. Ninety percent of doctors, 60% of clinical officers, 14% of nurses and 24% of midwives who worked in accredited ART clinics reported that they prescribe ART (p<0.001). Sixty-four percent of the people who prescribed ART were not doctors. Among professionals who prescribed ART, 76% of doctors, 62% of clinical officers, 62% of nurses and 51% of midwives were trained in initiating patients on ART (p=0.457); 73%, 46%, 50%, and 23%, respectively, were trained in monitoring patients on ART (p=0.017). Seven percent of doctors, 42% of clinical officers, 35% of nurses, and 77% of midwives who prescribed ART assessed that their overall knowledge of ART was lower than good (p=0.001).[[6]](#endnote-7)

While such MLP represent a primary segment of the healthcare workforce in Uganda and elsewhere, the medical officer is still most often identified as the recipient of coordinated training activities. With appropriate training, however, MLP have been shown to successfully deliver antiretroviral therapy to HIV patients in Kenya,[[7]](#endnote-8) Malawi,[[8]](#endnote-9) Mozambique,[[9]](#endnote-10) [[10]](#endnote-11) Rwanda,[[11]](#endnote-12) and Zambia.[[12]](#endnote-13) [[13]](#endnote-14) Because MLP are less likely than physicians to migrate toward higher paying jobs in the developed world, have shown competence in delivering services normally reserved for medical officers, and are already providing antiretroviral care in many parts of Africa, they may well be the most valuable existing resource in Africa to deliver ongoing care of infectious diseases.

**Existing training programs are inefficiently aligned with vertical disease programs.** In Uganda, training activities for all cadres of healthcare are often provided by international entities and non- governmental organizations that function independently, outside of the MOH planning framework. Such training efforts are most often conducted through isolated disease-specific programs, creating expensive redundancies even while training programs remain fragmented and incomplete. Even programs like PEPFAR, the Global Fund to Fight AIDS, Tuberculosis and Malaria, and the President’s Malaria Initiative provide support vertically by disease, creating inherent inefficiencies for human capacity-building efforts. And while HIV/AIDS, malaria and tuberculosis combined account for 29% of mortality in developing countries, illnesses such as acute respiratory illness, diarrhoeal disease and measles account for a slightly greater number of deaths (30%).[[14]](#endnote-15)

**Information regarding the most cost-effective way to train MLP to deliver quality care of infectious disease is critically needed.** Despite evidence suggesting that knowledge gained through intensive classroom training courses is not fully applied once the trainee returns to his/her real-world clinical setting,[[15]](#endnote-16) and that on-site training[[16]](#endnote-17) and supervision[[17]](#endnote-18)can favourably impact clinical practice, investment in human capacity-building continues to be concentrated on classroom training with little or no follow-up reinforcement. The status quo persists in part because of the lack of documented cost-effectiveness analysis of more costly on-site support services. Little is done to integrate or evaluate these supplemental training efforts, and training programs vary considerably in course content, duration, target recipient, and delivery mechanisms.

Experts in global health are calling for increased funding for training of MLP, and stressing the need for large donors to incorporate task shifting into their funding plans. Amid recognition that poor adherence to medication and undetected treatment failure can lead to pathogen resistance, however, much care is needed to ensure that MLP are well prepared to provide quality care. The development community seems poised to expand training efforts exponentially to address mid-level healthcare providers – who outnumber doctors in Africa by at least 6 to 18 – without the prerequisite understanding of which training approaches yield the best and most lasting results. Evidence for effective approaches is therefore much needed.

# CHAPTER TWO: RESEARCH PROBLEM

## 2.1 Problem Statement

Little has been done to test the effectiveness of disparate approaches to improving healthcare service delivery through human resource development. As the global health community seeks to expand training efforts to address mid-level healthcare providers (nurses and clinical officers) rigorous evaluation of which training approaches yield the best and most lasting results is needed to know what type of training program to implement or fund.

## 2.2 Significance

**The principal output of this evaluation will be a proven model of an integrated capacity-building package for the care and prevention of infectious disease in Africa.** The package will include a single curriculum for MLP and a portfolio of on-site support services founded on Accordia Global Health Foundation’s considerable experience in training clinicians in North America and Africa.

**IDCAP will train 72 MLP and 432 multidisciplinary team members at 36 sites throughout**

**Uganda.** These sites serve a catchment area of approximately 17% of the country’s population.

**Box 1. Uganda’s Public Health Facilities**

11 Regional Referral Hospitals – 2,000,000 served per hospital

55-70 District Reference Hospitals – 500,000 served per hospital

150-200 Health Center IV (primarily clinical officers and nurses) – 100,000 served per center

900-1000 Health Center III (primarily clinical officers and nurses; no lab services) – 20,000 served per center

**The population in the areas surrounding the proposed sites will benefit directly from lower infection, illness and mortality rates.** The improved ability of clinic staff to deliver quality prevention and care services will increase access to cost-effective interventions delivered according to national guidelines by 9% to 25% depending on the intervention.

**IDCAP will provide definitive evidence on the cost-effectiveness of on-site support.** The results on the cost-effectiveness of on-site support services including Continuous Quality Improvement (CQI) activities and on-site training for multidisciplinary teams) could potentially encourage investment away from up-front classroom-based training programs, and toward the workplace capacity building programs widely suspected to have more long-lasting results.

**Results of this evaluation will enable more efficient use of donor investment.** This evaluation seeks to identify the nature of the ideal capacity-building program for MLP in Uganda, enabling the considerable amount of global resources to focus on its replication throughout Africa and the developing world. Large donors will be encouraged to support the whole or a portion of an integrated infectious disease training program rather than disease-specific training approaches currently being employed. Demonstration of achieved competence in treating and preventing multiple infectious diseases will hopefully dissuade donors from continuing the currently inefficient and redundant efforts found in disease-specific training programs.

## 2.3 Research Question

Two sets of questions will be addressed.

1) Is an Integrated ID Training course (classroom and distance learning) for mid-level practitioners effective at building the skills required to perform key clinical tasks at acceptable standards? To answer this question, 2 mid-level practitioners from each of 36 sites will be invited to a Core Infectious Diseases course at IDI. The unit of analysis will be the individual. The evaluation design will be a before/after comparison of trainee skills and performance.

2) Does Onsite Multidisciplinary Team training and Continuous Quality Improvement activities, which is called On-Site Support (OSS), significantly improve clinic performance and health outcomes? If yes, are the OSS activities cost-effective? To answer these questions, 36 sites will receive the OSS activities for nine months, but 18 will be randomly assigned to receive the OSS in phase 1 and the others will receive it nine months later. The unit of analysis will be the site, and the evaluation design is a randomized trial of sites on key performance indicators.

## 2.4 Objectives

### 2.4.1 General ‘

To evaluate the effectiveness of an integrated training program for mid-level practitioners on the care and prevention of infectious diseases, and the incremental impact and cost-effectiveness of on-site support services, through their randomized and staggered introduction at 36 sites in Uganda in order to identify a cost-effective way to build capacity of mid level practitioners in sub-Saharan Africa for the care and prevention of infectious diseases

### Specific objectives

1. Evaluate the effectiveness of the integrated Infectious Disease Training in preparing mid-level practitioners to perform key clinical tasks corresponding to infectious disease competencies at acceptable standard
2. Evaluate the effectiveness of on-site support services (OSS) in improving clinic performance
3. Estimate the cost-effectiveness of site support services
4. Compare two methods for estimating cost-effectiveness: a) economic modeling in which effectiveness is measured by original data on performance indicators at 36 sites and published estimates of the effect of the performance indicators on Disability Adjusted Life Years (DALYS), and b) estimates in which effectiveness is measured original verbal autopsy data on mortality among children five years or less.
5. Evaluate the effectiveness of bi-monthly OSS for six months on clinical performance at Phase 1 sites after monthly OSS for nine months during Phase 1.

##

# CHAPTER THREE: METHODOLOGY

## 3.0 Overview

##

There are four major components of the evaluation design as described below: 1) Site Assessment, 2) Competence and practice of individual MLP who participate in IDT, 3) Facility cost and performance indicators, and 4) Mortality survey. The site assessment guided the curriculum development and site selection. As shown in Figure 1, it occurred only once in Year 1. The competence and practice of individual MLP will be evaluated with methods that are currently used by the Infectious Diseases Institute (IDI) to evaluate trainees. Data on MLP will be collected three times: a) before training, b) after the three-week course, and c) after the nine-month program that includes two, one-week booster courses and distance learning. Facility performance indicators will be collected on a monthly basis from each site. Data for external quality assurance of laboratory performance will be collected at baseline and end of the intervention or analyzed as secondary monthly data from the Tuberculosis National Reference Laboratory. Sites will be randomly assigned to begin OSS in either Phase 1 or Phase 2 and the facility indicators of these two samples of sites will be compared. The principal investigators of IDCAP are actively considering collecting data on mortality among children under five, but a final decision has not been made. At the request of the acting chairperson of SOMREC, we are including information about this potential activity. Mortality surveys would be conducted before and after the OSS. In this chapter, each component of the evaluation is described separately.

**Figure 2: Evaluation Design**

The indicators that will be collected from components 2-4 are summarized in Table 1. No indicators were collected for the Site Assessment.

|  | **Table 1 Summary of Indicators** | | | |  | | | | | |
| --- | --- | --- | --- | --- | --- | --- | --- | --- | --- | --- |
|  | | Hypothesis 1: Build clinical skills of core course trainees | | Hypotheses 2-4: Test effectiveness of on-site multidisciplinary training and continuous quality improvement | | | | | | |
|  | | Com-petency | Practice | Process indicators | | Laboratory Performance | Clinical Performance (examples) | Modeling health outcomes | | Direct measure of health outcomes or mortality |
| Effective Coverage | Cost-effective intervention (from literature) |
| HIV prevention | | Measured by case studies or case scenarios | Measured by observation of trainees at their site | 1) Staff on-site  2) Employee engagement,  3) Availability of supplies, including   - HIV test kits - cotrimoxazole - first line ART - TB drugs - coartem - reagents for laboratory tests | | HIV test  DBS | % HIV positive pregnant women with an HIV/ART card  % HIV exposed infants on CTX | Number of pregnant women with HIV who are referred to PMTCT | PMTCT | HIV exposed children who are HIV- |
| HIV care | | Blood test  Urine test  CD4 specimen | Number of HIV+ patients prescribed daily cotrimoxazole | Number of HIV+ patients on cotrimoxazole therapy | Daily Cotrimoxazole | Mortality of HIV patients |
| ART | | Number of ART naïve HIV+ patients who are eligible for ART who start 1st line ART | Number of HIV patients on ART | ART | Mortality of ART patients |
| TB/HIV | | HIV test  Sputum smear | Number of TB suspects with known HIV status  Number of TB/HIV patients started on ART within 3 months of starting TB treatment | Number of patients who are smear negative or extra-pulmonary TB detected & cured under DOTS | Full DOTS | Mortality of TB/HIV patients |
| Case mgmt of respiratory illness | | Sputum smear | Number of TB suspects sent for first AFB smear  Number of smear negative TB suspects started on empiric treatment | Number of TB patients detected and cured under DOTS  Number of children diagnosed with pneumonia | - DOTS - Case mgmt of pneumonia for children | Mortality of TB patients  and children under 5 |
| Case mgmt of fever | | Malaria smear | % of malaria suspects sent for blood smear  % of smear negative patients treated with any antimalarials | Number of patients with a positive laboratory test for malaria (blood smear) who are treated with ACT | Case management with ACT | Mortality of children under 5 |
| Emer-gency treatment and triage | |  | Number of patients triaged on a random sample of days |  |  | Mortality within 24 hrs of admission |

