The exception is patients with HIV. The indicators on mortality for HIV patients will be measured from a cohort of patients who come for a visit during the first three months after the OSS begins. They will be exposed to the minimal risk of loss of confidentiality and asked to give verbal consent for IDCAP to follow their health status for 24 months. Contact information that is reported on HIV/ART cards will be collected. These patients will be asked to check with the evaluation clerk at the site each month when they come for a monitoring visit during treatment and report whether they are working and/or performing normal activities. At the end of phase 1 and 2, they will be offered a transportation refund for travel to the clinic for a total of two payments even if they complete or stop treatment. If the patient misses a monthly visit, the evaluation assistant will use the contact information to find out whether the patient has transferred out, stopped treatment, become bed-ridden or died.

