### 3.4.2 Design

For the second cost-effectiveness analysis, an alternative measure of effectiveness will be years of life saved. Population-level data is the only valid way to directly measure the effect of the intervention on health outcomes.

It is expected that the capacity-building and quality improvement interventions will reduce mortality by improving the emergency triage and treatment of patients and improving the quality of care for infectious diseases. The Uganda Child Verbal Autopsy Study showed that 75% of children who died received care from a government or private hospital or health center.[[35]](#endnote-36) Given that these children had access to care, it may be possible to save their lives by improving the quality of that care.

When the quality of care improves, utilization of a health facility increases.[[36]](#endnote-37) [[37]](#endnote-38) If the quality of care improves at the Phase 1 sites, they are likely to attract more patients including sicker patients. Paradoxically, as the quality improves the mortality of patients at the facility may increase, because the volume of patients and case complexity increases. Population-level data at the Phase 1 sites would reveal that population-level mortality had decreased because more people are seeking care, even if facility-level mortality increased.

UBOS proposed estimating population-level mortality with a two-part sampling method that builds on recent advances in the Demographic Surveillance Systems in which representatives of local council members at the parish level provide information about recent deaths. Although vital records systems may not be reliable in many African countries, there is a policy in Uganda for citizens to report births and deaths to the local council members. The information is more reliable in rural parishes than urban.

In the first part, the local council member directs the interviewers to households where there is a “high index of suspicion” that a death of a child U5 has occurred. To ensure completeness, a listing of households in each enumeration area (EA) would be created from interviews with all households in collaboration with the local council member. The listing includes an identification number and location for each household, whether or not a death occurred within the household in the last 3 years, and if yes, the age of the person at the time of his/her death.

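### The ART row's mortality outcome is counted among patients on ART, a group OSS is meant to enlarge, and the protocol does not fix ART status before OSS begins

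*Protocol*

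**What the plan says.** Table 1 (section 3.0 Overview) lists, under Hypotheses 2-4, a direct health-outcome measure for each clinical area. For ART it is "Mortality of ART patients". In the same row the clinical performance indicator is "Number of ART naïve HIV+ patients who are eligible for ART who start 1st line ART" and the effective-coverage measure is "Number of HIV patients on ART".

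The Abstract states the contrast: "The effect of OSS on cost, clinical performance and health outcomes will be measured by a comparison of Phase 1 and Phase 2 sites".

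Section 3.3.5 (Consent, patients) says the HIV mortality indicators are "measured from a cohort of patients who come for a visit during the first three months after the OSS begins", with patients "asked to give verbal consent for IDCAP to follow their health status for 24 months". It does not say when, within that cohort, a patient is classed as an ART patient.

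Section 3.4.2 recognises the general difficulty: "Paradoxically, as the quality improves the mortality of patients at the facility may increase, because the volume of patients and case complexity increases". Its answer is population-level data, but the household survey in section 3.4.1 covers only children under five.

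**The concern.** Randomising sites makes the HIV patients of the two phases comparable only in groups whose membership OSS cannot alter. Being on ART is not such a group, since raising the number of eligible patients who start is one of the results OSS is judged on. If ART status is read after OSS begins, ART patients at Phase 1 sites include people who would not have started at a Phase 2 site. A difference in mortality between these groups then mixes the effect of OSS on survival with its effect on who is treated.

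At stake is the interpretation of one listed health outcome. It could show nothing, or point the wrong way, when OSS saves lives through additional ART starts. It could also flatter OSS if the extra starters are healthier than the usual ones.

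**Working it through.** The protocol states no event rate, effect size or power for ART-patient mortality; the site sample size in section 3.3.4 rests on two malaria indicators. There is no figure to reproduce. The check is a weighted average, and every risk in it is an assumption.

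**Notation.** c0 and c1 are the shares of eligible patients on ART without and with OSS. m_e is mortality of those on ART either way, m_n of those who start only because of OSS, and m_u of eligible patients left untreated. OSS is first taken to have no effect on m_e.

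- Mortality on ART: m_e without OSS; [c0·m_e + (c1 − c0)·m_n] / c1 with OSS.
- Mortality of all eligible: c0·m_e + (1 − c0)·m_u without OSS; c0·m_e + (c1 − c0)·m_n + (1 − c1)·m_u with OSS.
- Deaths averted: (c1 − c0)·(m_u − m_n).

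Mortality on ART therefore rises while total deaths fall whenever m_e < m_n < m_u.

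**Worked example.** Of 100 eligible patients, 50 start at control sites and 68 at OSS sites; m_e = 5%, m_n = 10%, m_u = 15%.

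- On ART: control 5.0%; OSS (50×5 + 18×10)/68 = 430/68 = 6.3%.
- All eligible: control (50×5 + 50×15)/100 = 10.0%; OSS (50×5 + 18×10 + 32×15)/100 = 9.1%.

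**Range.** Each cell gives mortality on ART with OSS, then deaths averted per 1000 eligible.

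| Assumed m_e / m_n / m_u | On ART without OSS | c0/c1 = 50/60% | 50/80% | 30/70% |
| --- | --- | --- | --- | --- |
| 5 / 12 / 20% | 5.0% | 6.2%; 8 | 7.6%; 24 | 9.0%; 32 |
| 5 / 8 / 15% | 5.0% | 5.5%; 7 | 6.1%; 21 | 6.7%; 28 |
| 5 / 5 / 20% | 5.0% | 5.0%; 15 | 5.0%; 45 | 5.0%; 60 |
| 8 / 5 / 20% | 8.0% | 7.5%; 15 | 6.9%; 45 | 6.3%; 60 |

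The first two rows reverse the sign. The third shows no effect while 15 to 60 deaths per 1000 are averted. The fourth does not reverse, but its fall comes only from a changed mix of patients.

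**Dilution by existing ART patients.** Adding an assumed 200 patients already on ART at 5% in each arm to the worked example gives (250×5 + 18×10)/268 = 1430/268 = 5.3% with OSS, against 5.0%.

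**If OSS also improves care of usual starters.** In the worked example the two arms tie when (50x + 180)/68 = 5, so x = (340 − 180)/50 = 3.2%. With the 200 existing patients, and the same improvement applied to them, the tie is at x = (1340 − 180)/250 = 4.64%. A smaller improvement than that would still look like harm.

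**The case against.** The case on the other side is substantial, and several parts of it stand.

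- **The table entry is a label, not an analysis.** It names no date for ART status and no model, and an analysis plan may supply them. This stands as a limit: if ART status is fixed at cohort entry, later starts cannot enter the denominator. Only starts in the three-month entry window after OSS begins could then bias it. A reader might infer that the bias is present however the cohort is fixed; the documents do not support that. They also do not remove the risk, because entry itself follows the start of OSS and no section fixes ART status earlier.
- **Deaths among eligible patients who never start ART are not lost.** A reader of the ART row alone might infer that they are. The HIV care row of Table 1 lists mortality of HIV patients with no ART condition, and the section 3.3.5 cohort traces those who miss visits. Those deaths count there. The ART row remains a separate listed outcome with its own denominator.
- **Reversal is not predicted.** It needs the extra starters to have higher mortality than usual starters, and too little gain among the latter to offset it. The protocol gives no rates, and sites had to be active or soon-to-be-active ART sites (section 3.1.3), so existing patients may dilute the effect.
- **Nothing central depends on it.** The primary regression in section 3.3.2 uses performance indicators. Cost-effectiveness uses performance indicators with published DALYs, or under-five deaths.
- **Switching to patients eligible at entry is not a clean repair.** CD4 specimens are an OSS laboratory indicator, so recorded eligibility may itself respond to OSS. This stands and shapes the fix.

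**Conclusion.** The point holds in a limited form. The ART row's between-phase outcome has a denominator that OSS is meant to enlarge, and the protocol does not fix ART status before OSS begins. If later starters are counted, the contrast is confounded by who starts ART and can hide a benefit, show apparent harm or flatter OSS.

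The direction and size cannot be derived from the documents. The worked 1.3-point excess (6.3% − 5.0%) rests wholly on assumed risks and falls to about 0.3 points (5.3% − 5.0%) with 200 existing ART patients per arm. The stronger inference, that OSS will appear to raise mortality, is not supported. The outcome is secondary, and the primary analysis is unaffected. It is still worth correcting, because section 3.4.2 accepts that improving quality can raise facility mortality and its population-level remedy does not cover ART patients.

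**What to change.** 1. Make the HIV care row's mortality indicator the between-phase comparison for HIV: all cohort members, by randomised phase of their site, whether or not they start ART.
2. For the ART row, compare mortality only within groups defined by ART status and, where recorded, eligibility on the HIV/ART card before OSS began. Use the same rule in both arms, with the start of Phase 1 OSS as the common date so that Phase 2 patients are not classified nine months later.
3. Report mortality among everyone on ART as descriptive, with no between-phase inference.

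The cost is a change to one Table 1 entry and a sentence on when status is fixed. Section 3.3.1 already provides for extracting the HIV/ART cards, and the cohort is already followed. The downside is fewer patients in the ART-row comparison, and eligibility may be incompletely recorded before OSS. One limit remains: the cohort in step 1 is still enrolled after OSS begins, so any early effect of OSS on who attends is not removed and should be acknowledged.
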